## 8.3. Study procedures

### 8.3.1. *Description of the vestibular tests which will be conducted*

#### **Caloric test**

The caloric test uses temperature to create fluid flow inside the SCCs which results in deformation of the cupola and subsequent increased or reduced firing of the SCC nerves. This results in an eye movement response which is captured with ENG. A change in temperature is achieved by irrigating the ear canal with water of a specific temperature. It is one of the most used tests clinically to assess VOR response. Eye movement calibration is performed before each irrigation. Patients are positioned in a supine position with their head tilted 30° from the horizontal plane. Each irrigation lasts 30 seconds with a volume of at least 250 mL water for cold (30°C) and warm (44°C) irrigations. A 5 minute stimulus interval is kept between irrigations.

#### **Dynamic visual acuity test (DVA)**

The DVA test is described in the article by Guinand et al.. It is aimed at measuring a functional aspect of VOR: visual image stabilization while walking. The DVA test consists of the patient walking on a treadmill, walking at different walking speeds, with or without holding the handrails. While walking, they will perform a visual acuity test by reading out Sloan optotypes (CDHKNORSVZ) displayed in decreasing size on a computer screen in front of the patient. Using an adaptive up-down staircase procedure, the LogMAR

of each patient is determined. LogMAR (logarithm of Minimal Angle of Resolution) is used as an estimate of visual acuity. Patients are also tested in static condition (while standing still) to serve as a reference. The test takes around 10 minutes, depending on the patient.

Since the patients are walking under controlled conditions on a treadmill, this moment is also taken to assess gait. Two MOX physical activity monitor accelerometers are attached to the patient's upper leg and lower back so the movement the lower limb and center of mass can be observed. The data obtained from these MOX sensors serve as complementary to the full gait analysis performed at a different moment. The addition of these accelerometers do not influence the patients gait and therefore will not influence the outcome of the DVA.

When DVA is measured during the baseline testing day, a maximum safe walking speed will be established. This speed will also be used during the prolonged stimulation period to be able to compare visual acuity. During the DVA tests conducted within the prolonged stimulation period one additional measurement is added to the DVA test. While the patient is using the treadmill for the DVA measurement, the patient will also again be asked to walk at their maximum safe walking speed. The change in walking speed will also be taken as an outcome parameter to indicate an increase in dynamic balance.

### ***3D Head impulse test (3D HIT)***

The HIT is one of the standard tests performed daily as a diagnostic tool for patients with vestibulopathy in our clinic. The test is designed to quantify VOR at its fundamental level by measuring eye moment (gain and direction) as a response to passive high velocity head movements. It is performed along three different rotational axes: horizontal, right-anterior-left-posterior (RALP) and left-anterior-right-posterior (LARP). The patient is seated and fitted with VOG goggles to measure eye movements. The patient is asked to keep their eyes fixated on a target 1.5 meters ahead of them and to blink as little as possible. The examiner stands behind the patient and while holding the head of the patient, moves the head several times fast ( $>150^{\circ}/s$  for horizontal,  $>100^{\circ}/s$  for RALP and LARP) with a small amplitude ( $\pm 20^{\circ}$ ) randomly in either direction of one rotational axis. This is repeated for each rotational axis. Frequent brakes are taken between the head impulses to allow the patient to blink. Depending on the patient, this test takes around 20 minutes to complete.

### ***Functional head impulse test (fHIT)***

The fHIT is a variation of the 3D HIT, aimed at measuring the VOR at the same frequency as the 3D HIT, but at a more functional level. It quantifies how well a person can observe an image during high velocity passive head movements. The patient is seated and a gyroscope is fitted to the patients head by means of a head band. A screen is placed in front of the patient at a distance of 1.5 meters and the patient is asked to look at a fixation target shown on the screen. Before the start of the fHIT, the static visual acuity threshold is acquired by the fHIT system. After that, The examiner stands behind the patient and moves the patients head in the horizontal plane, in the same fashion as is done during the 3D HIT test (velocity  $>150^{\circ}/s$ , amplitude =  $\pm 20^{\circ}$ ). The gyroscope which is attached to the patient's head registers the head movement and a Landolt optotype ring is displayed for 80 ms on the screen, 80 ms after head movement velocity exceeds  $10^{\circ}/s$ . After the head movement the patient is asked to choose the orientation of the

Landolt ring from a set of 8 orientations by pressing the corresponding direction on a keyboard. The test is repeated 32 times (16 times per side) and takes around 10 minutes.

### ***Torsion Swing test***

The torsion swing test is aimed at quantifying the VOR response at a fundamental level, similar to the 3D HIT. However, with the torsion swing test the head movement stimulus has a smaller acceleration and a lower velocity compared to the 3D HIT. Therefore it quantifies the VOR response at a lower movement frequency. It is part of the standard tests performed daily as a diagnostic tool for patients with vestibular hypofunction in our clinic. The torsion swing test is performed using horizontal sinusoidal rotation (0.1Hz) with a peak velocity of 60°/s, while the subject sits in a rotating chair in complete darkness. Eye movements are recorded with VOG goggles fitted to the patients head. The test takes around 10 minutes to complete

### ***cVEMP and oVEMP***

Cervical vestibular evoked myogenic potentials (cVEMPs) and ocular vestibular evoked myogenic potentials (oVEMPs) are measurements of the VSR and VOR responses, respectively. They are routinely used in clinics and research to diagnose vestibular disorders due to their ability to selectively observe these reflex pathways at a fundamental level. The VEMP measurements are used to observe any residual vestibular function during the trial (if present).

cVEMPs are measured over the sternocleidomastoid muscle after stimulating the ipsilateral vestibular organ with multiple transducers: inserted earphones, bone conduction, galvanic stimulation (only at screening). Subjects are in a supine position with their back tilted in an angle of 30° from the horizontal plane and are asked to turn their head away from the location of the stimulus and to lift their head up slightly. A visual feedback system connected with a monitor ensures correct muscle contraction, measured with electromyography (EMG) software and self-adhesive electrodes. Two hundred EMG traces with a minimum mean rectified voltage (MRV) of 60 µV and a maximum MRV of 205 µV are accepted.

oVEMPs are measured over the inferior oblique muscle after stimulating the contralateral vestibular organ with the same stimulation parameters as for cVEMPs. Subjects are in a supine position and are instructed to keep their eyes fixed on a focus point 30 degrees behind the head to achieve superomedial gaze. A minimum of 300 EMG traces are accepted.

### ***Perception platform***

A hydraulic platform is used to measure the perceptual self-motion thresholds within each subject. A twelve-option paradigm, six translations and six rotations, is delivered by the platform. The subject sits in complete darkness in a chair mounted on the platform, fastened by a seatbelt, while wearing a blindfold and headset to mask visual and auditory cues. The six translations include motions in the horizontal plane (forward, backward, right, left) and in the vertical plane (up and down). The rotations includes yaw left, yaw right, pitch forward, pitch backward, roll left and roll right. Thresholds are found using a staircase protocol with a maximum duration of one hour. Motion trials starts at the highest possible acceleration and their directions are randomly chosen by the examiner. After each motion, the subject is asked to inform the examiner about the type and direction of the perceived movement. In case the subject can

indicate the correct type and direction of the movement, the stimulus is decreased with  $0.1\text{m/s}^2$  (translations) or  $10^\circ/\text{s}^2$  (rotations). In case of an incorrect response, the acceleration is increased with  $0.05\text{m/s}^2$  or  $5^\circ/\text{s}^2$ . If the subject then could indicate the correct type and direction of movement, the acceleration is decreased with  $0.03\text{m/s}^2$  or  $3^\circ/\text{s}^2$ . A double confirmation of the lowest threshold combined with double incorrect responses at the acceleration one step below threshold, is considered the perceptual self-motion threshold for that motion profile.

### ***Gait and balance tests***

To observe the VSR response at a functional level, patients will complete a number of walking trials on the computer assisted rehabilitation environment (CAREN) system to assess their walking patterns, stability and biomechanics during various tasks. It allows for the quantification of biomechanical measures such as stepping behavior, gait stability and gait variability.

The CAREN is a dual belt treadmill system with a 6 degree of freedom motion platform and a 180 degree virtual reality environment. Reflective markers will be placed on anatomical landmarks and will be recorded via the system's 3D motion capture system. Additionally, two MOX accelerometers will be placed on the lower back and thigh to record lower limb and center of mass accelerations during the tasks.

At the beginning of the session, the system and set-up will be explained to the patients, as well as the measurement protocol. The session will start with familiarization trials, during which the patients will walk on the treadmill for short periods at multiple speeds to become accustomed to walking on the system. During all sessions, the subjects will be secured with a safety harness connected to an overhead frame. The CAREN operator will ensure that the subject's knees cannot reach the ground and that the subject cannot walk too far to the front or back of the treadmill. The exact amount and characteristics of the familiarization period is flexible due to the heterogeneous nature of the patient group and their various experiences with treadmill walking. Once the CAREN operator, patient and clinical researcher are in agreement that the patient is comfortable and familiarized to the set-up, the measurement will be conducted. These measurements include walking at different speeds in combination with different perturbations of the walking platform. Standardized questions will be included regarding effort, fatigue and difficulty for each task to allow comparison between what the patient perceives during the measurements and their gait performance.

Beside the walking trials on the CAREN system, patients will also complete a set of clinical balance and gait tests (e.g. the mini-balance evaluation systems test (mini-BESTest)). Clinical balance and gait tests are often used as a diagnosis tool or to assess progression during physiotherapeutic treatment in clinics. They allow for the functional characterization of both gait and balance during walking and standing, offering insights into the VSR at a more functional level than the walking trials on the CAREN system. By including both types of tests, a more complete characterization of any potential change in gait and balance caused by vestibular stimulation can be performed.

### ***Costas array-based experiment***

To assess the fundamental response of the brain to SCC nerve stimulation, a Costas array-based experiment will be conducted. The results of this experiment will give valuable insights in how the brain

processes electrical stimulation and will allow for the development of more optimized stimulation algorithms. The experiment consists of stimulating the SCCs with a signal based on a Costas array. This will induce eye movements, which will be recorded using VOG while the patient sits in a completely dark room. The exact response of the eye movements is correlated with the input signal, allowing for the exact evaluation of the eye movement response to a signal with stimulation intervals that are fully uncorrelated to other parts of the original signal.

### ***Evoked Vestibular Brainstem Response***

The electrically evoked vestibular brainstem response (eVBR) is the response of the vestibular nerve as a result of electrical stimulation, all the way up to the brainstem, equivalent to the well-known auditory brainstem response (ABR). The vestibular implant will be used to evoke the response, making it possible to quantify the response, and potentially relate it to VI output. This not only gives a fundamental insight in the processing of vestibular information by the vestibular nerve and related brainstem areas, but proving this concept might open doors for applications as intra-operative electrode positioning verifications and using it as basis for CVI fitting, where it is contrary to the VOR and VEMP not impaired by anesthesia or patient cooperation.

An eABR equivalent setup will be used, consisting of a system controlling the CVI stimulation (the clinically used MAESTRO software controlling the MAX-box (both by MED-EL, CE-approved)) and a system designed for measuring ABR (the clinically used Surpass (EMS medical, CE-approved)). Responses will be measured on the three vestibular electrodes (eVBR) and a selection of the cochlear electrodes (eABR). The subject is asked to lay fully relaxed, and does not need to do anything during the test. Intersubject variability and the reproducibility of the traces will be used as main outcome measure for the feasibility of the method. Stimulus related effects are determined by a step-wise change in stimulus characteristics, e.g. stimulus amplitude.

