##### 13.1.4. *Selectivity of the mechanism*

Due to the CVI being based on electrical stimulation, current spread will occur. As the stimulation current increases, so does current spread, which may lead to stimulation of other nerves such as facial nerves or auditory nerves. The potential for stimulating nerves outside of the inner ear is reduced due to the way the stimulation parameters are chosen, setting the maximum stimulation currents below the current at

which unwanted stimulation occurs (see chapter 8.3.2). This is the same way as current spread is reduced with a CI. Part of the study is to safely investigate the presence of interfering current spread between the cochlea and the vestibular system. The interaction between vestibular and cochlear stimulation might (temporarily) result in a reduced CI or VI performance. The patient will be informed that CI performance might be reduced during simultaneous stimulation, since this might result in a burden to the patient. This will only be the case while the VI-part is active during the VI fitting period and the prolonged stimulation period. While optimizing the VI stimulation response during the VI fitting, the goal is to minimize the interaction between CI and VI stimulation and therefore minimize this burden.

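### The feasibility outcome for the evoked vestibular brainstem response does not identify the nerve, so a repeatable non-vestibular trace can satisfy it

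*Protocol*

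**What the plan says.** Section 8.3.1 (Evoked Vestibular Brainstem Response) defines the quantity of interest by its source: the eVBR "is the response of the vestibular nerve as a result of electrical stimulation, all the way up to the brainstem". On recording it says: "An eABR equivalent setup will be used". Traces are taken from the three vestibular electrodes (as eVBR) and from some of the cochlear electrodes (as eABR).

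The feasibility outcome is then fixed: "Intersubject variability and the reproducibility of the traces will be used as main outcome measure for the feasibility of the method". Next to it stands a plan to vary the stimulus: "Stimulus related effects are determined by a step-wise change in stimulus characteristics, e.g. stimulus amplitude". A link to implant output is mentioned only as a possibility, the set-up "making it possible to quantify the response, and potentially relate it to VI output". No comparison of eVBR with eABR, and no agreement with a vestibular threshold, forms part of the outcome.

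Elsewhere, section 13.1.4 states that current spread grows with stimulation current and "may lead to stimulation of other nerves such as facial nerves or auditory nerves". Section 1.4.6 cites interaction between vestibular and cochlear electrodes in a similarly designed implant. Section 10.4 allows that some vestibular electrodes may fail to give a vestibular response.

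**The concern.** The claim to be tested concerns one nerve, and the outcome chosen to test it is indifferent to the nerve. Any stimulus-locked response repeats from one average to the next, whether it comes from the vestibular nerve, the auditory nerve or a muscle driven by the facial nerve. The set-up is built for auditory brainstem responses, and the patients must be cochlear implant candidates (section 4.2.2) without indications of a poorly functioning cochlear nerve (section 4.3.1). An excitable auditory nerve is therefore to be expected.

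At stake is what a favourable feasibility result would mean. Section 8.3.1 names two possible later uses: verifying electrode position during surgery and guiding the fitting. For the first, the weakness points in an awkward direction. Section 13.1.11 says that an electrode misplaced by a few millimetres needs substantially more current, and more current means more spread. A repeatable trace could then come from the very electrode that the method is meant to flag.

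**Working it through.** The protocol gives no threshold, error rate or sample size for the eVBR, so there is no figure to reproduce. The check asks whether each planned measure would differ between a vestibular and a non-vestibular source.

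1. **Reproducibility.** Write replicate average *j* on one electrode as v(t) + a(t) + e_j(t), where v is the vestibular part, a is the part from other nerves, and e_j is independent noise with variance N². With S² the variance of v + a over the recording window, the expected replicate correlation is about S²/(S² + N²), that is SNR²/(1 + SNR²) with SNR = S/N. If a = 0, S² is the vestibular variance; if v = 0, it is the non-vestibular variance. The formula is the same. At SNR 1, 2 and 4 it gives 1/2 = 0.50, 4/5 = 0.80 and 16/17 = 0.94 for either source, and 0 with no response. These SNR values are illustrative assumptions, not estimates for this trial. Reproducibility separates a response from noise, but not one nerve from another.

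2. **Intersubject variability.** This is the spread of a trace feature across patients, for example SD/mean of amplitude. An auditory response has such a spread just as a vestibular one does. The protocol states no range expected for one and not for the other, so no observed value points to the source.

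3. **Stepwise stimulus change.** Growth with amplitude is expected of a vestibular response. By section 13.1.4 it is also expected of spread. Growth alone does not discriminate; the level at which the response first appears might.

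4. **Can the confounder occur here?** Section 13.1.4 says that maximum currents are set below the level causing unwanted stimulation, and that this reduces stimulation of nerves outside the inner ear. That helps against facial-nerve responses. Spread between cochlea and vestibular system is treated in the same section as something the study will investigate, so it is not ruled out. Together with section 10.4, an electrode with an auditory trace and no vestibular response is a possibility that the protocol itself allows.

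5. **What planned data could discriminate?** Section 8.3.6 (VI fitting) sets a threshold T for each vestibular electrode from perception, VOR or VSR, whichever appears at the lowest current. The eABR gives a within-patient auditory reference. On timing, the example fitting schedule (Table 3, section 3.2) places VBR at the end of day 1. The third canal is first fitted on day 2, and the second fittings run over days 2 and 3. Final thresholds therefore do not exist when VBR is recorded, and the comparison has to be retrospective.

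6. **Amount of data.** With 8 to 13 patients and three vestibular electrodes each, there are 3 × 8 = 24 to 3 × 13 = 39 electrodes at most.

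**The case against.** The strongest reply is that this is a first look at a new recording technique in a trial that section 10 calls exploratory. Asking first whether traces can be obtained repeatably is a legitimate feasibility question. The eABR, stimulus steps and fitting thresholds are all collected, and how they are combined could be left to the definitive statistical plan. The later uses in section 8.3.1 are worded as prospects, not decisions.

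Much of this stands. It limits the weight of the point and supports keeping reproducibility as a quality measure. It does not remove the point, because section 8.3.1 does not leave the outcome open: it names the main feasibility measure, and that measure is non-specific.

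Three stronger readings are tempting, and the protocol supports none of them.
- A reader might infer that the method will be declared feasible without any vestibular response. No pass mark or decision rule is stated, so only *can* is justified.
- A reader might want a false-positive percentage. It would need a signal-to-noise ratio and a correlation cut-off, and the protocol gives neither.
- A reader might infer that a trace resembling the eABR is thereby shown to be auditory. Section 8.3.1 presents the eVBR as the counterpart of the auditory response and gives no distinguishing latency or shape. Resemblance leaves the origin unknown; it does not settle it.

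**Conclusion.** The point holds in limited form. Both named measures are blind to the source of the trace, and the protocol describes a mechanism that could produce a repeatable non-vestibular one. Meeting the outcome as written would show that a stable response can be recorded from a vestibular electrode, but not that it is vestibular.

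The size cannot be quantified from the protocol. The conclusion rests on two premises: that spread can evoke a stimulus-locked response at the levels used, which section 13.1.4 allows, and that repeat averages differ only by noise. The consequence stays within the eVBR experiment. It is absent from Table 6 and feeds neither the DVA outcome nor the sample size calculation in section 4.4. This is a worthwhile improvement, not a defect that threatens the trial.

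**What to change.** Add evidence of vestibular origin to the feasibility outcome in section 8.3.1:

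- Name amplitude as a stimulus characteristic to be stepped; it is now given only as an example. For each vestibular electrode, report whether a replicated response is present and the lowest level at which it appears.
- Compare that level, retrospectively, with the electrode's final T or VOR threshold from fitting, and state which response defined T.
- Prespecify a comparison of latency, morphology and amplitude growth with the same patient's eABR. Class traces that cannot be told apart from it as *origin undetermined*: not negative, but not counted as support for feasibility either.
- Report the number of electrodes with a concordant response out of those tested, with an exact interval. Three electrodes share a patient, so show the counts per patient as well and read the electrode-level interval as descriptive.
- Keep reproducibility and intersubject variability as measures of recording quality.

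The cost is a few lines of protocol text and some extra trace analysis. Thresholds and eABR traces are already planned, and the schedule need not change. The downside is that fewer electrodes will count as showing a vestibular response.
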